#### Primary outcomes

The primary outcome is the patient’s score on the PROMIS Anxiety 4a Questionnaire and on the PROMIS Depression 4a Questionnaire, as well as on the GAD-7 and PHQ-8 scales 1 month before surgery, on the day of the surgery, and 1, 2, and 3 months after surgery, to assess the severity of the patient anxiety and depression levels and the potential effect of RxWell™ on these conditions (Table 1).

The short PROMIS 4a questionnaires are 4-item forms with five-response options per question ranging in value from one to five. The lowest possible raw score is 4, and the highest possible raw score is 20. In both cases, a higher score indicates worse status, and both assess the condition over the past 7 days. The PROMIS Anxiety instruments measure self-reported fear (fearfulness, panic), anxious misery (worry, dread), hyperarousal (tension, nervousness, restlessness), and somatic symptoms related to arousal (racing heart, dizziness). The PROMIS Depression instrument measures self-reported negative mood (sadness, guilt), views of self (self-criticism, worthlessness), social cognition (loneliness, interpersonal alienation), and decreased positive effect and engagement (loss of interest, meaning and purpose). The PROMIS scores are centered with a mean of 50 and standard deviation of 10. The *T*-score range for severe anxiety is > 70, moderate 60–69, mild 55–59, and < 55 is none to less anxiety. Based on our prior work, we chose a baseline anxiety and depression mean *T*-score of 60, with a standard deviation of 10.

The Generalized Anxiety Disorder (GAD-7) is a 7-question instrument that measures self-reported anxiety, worry, trouble relaxing, restlessness, irritability, and fear in the last 2 weeks [32]. The Patient Health Questionnaire (PHQ-8) is an 8-question instrument that measures self-reported interest and pleasure, irritability and depressed mood, problems with sleep, appetite and concentration, lack of energy, changes in the speed of movement and speech, and low self-esteem, over the last 2 weeks [33]. In both questionnaires, there are options for each question, ranging from 0 to 3, and in all cases, a higher score indicates a worse status. The lowest possible score is 0 and the highest total score is 21 for GAD-7 and 24 for PHQ-8.

#### Secondary outcomes

Pain catastrophizingSleep disordersFatigueAbility to participate in social rolesPain interferencePerioperative pain at rest and during movementOpioid requirements and opioid morphine equivalents,Functional recovery, andResource utilization associated with surgery and recovery (hospital length of stay, duration of physical therapy). We will adjust for surgical decision during the resource utilization modeling as surgeons vary in their decision algorithms for patient discharge timing.

In addition, as part of secondary outcomes, we will record participants’ usage of RxWell, adherence, use frequency, number of techniques completed, and the path in the RxWell platform (anxiety vs. depression) the patient is utilizing. Participants will also complete a satisfaction survey at the end of their participation. The instruments and specific timepoints at which these outcomes are measured are collected in Table 1. The study team will receive monthly reports providing the number of techniques completed, the number of messages to the coach, and the program used in *RxWell* (anxiety vs. depression).

The tools used are as follows:Pain catastrophizing—Pain Catastrophizing Scale [34]Sleep disorders—PROMIS 29+2 [35]Fatigue—PROMIS 29+2 [35]Ability to participate in social roles—PROMIS 29+2 [35]Pain Interference—PROMIS 29+2 [35]Perioperative pain at rest and during movement—pain medications [36]

#### Plans for assessment and collection of outcomes

The study coordinators undergo a week of orientation towards patient screening, approach to patients, and applying the questionnaires. The study coordinators evaluate the data for any quality issues such as duplicate measurements. The questionnaires are validated in prior work [32, 33, 37].

#### Other variables of interest

At baseline, participants will also complete a demographic, lifestyle, and diagnostic survey, consisting of age, gender, ethnicity, race, height, weight, smoking and alcohol use, medical history, ongoing treatments, and comorbidities.

The following medical data will be gathered: type of operation, surgical indication, and American Society of Anesthesiologists (ASA) classification and if the patient received a nerve block before the surgery.

### Study interventions

#### SuRxgWell Trial (the use of RxWell™ among orthopedic surgery patients—digital Cognitive Behavioral Intervention)

The dCBI is a mobile application that guides patients through a series of cognitive behavioral intervention learnings and techniques such as relaxation, cognitive reframing, exposure, and mindfulness. The RxWell™ digital behavioral tool offers a patient access to a live coach via an asynchronous text messaging component within the application. This personalized experience helps guide and motivate the patient through the program and to apply the techniques into everyday life situations. The application provides feedback and progress to the patient. Feedback includes tracking depression and anxiety from Generalized Anxiety Disorder Scale (GAD) and Patient Health Questionnaire (PHQ) measures that are completed within the app. Coaches review messages and scores within 2 business days. In the event of a risk escalation, coaches will email the coach supervisor and include “urgent” in the subject line to notify the supervisor of a high-risk situation or of an interaction with a user where they encounter concerning symptoms. Concerning symptoms may be exhibited either within the context of a message sent to the coach or free text responses within techniques.

This application guides patients through a series of CBT learnings and techniques such as relaxation, cognitive reframing, problem solving skills, distress tolerance, and mindfulness. These techniques are brief and interactive with easy-to-use material presented as audio, video, and interactive text content. The application includes two different pathways, one focuses on anxiety and one on depression management. The participant will utilize one of the programs depending on the initial psychological assessment. If participants score ≥ 60 on the PROMIS Anxiety questionnaire, they will follow the Anxiety Pathway, and if participants score ≥ 60 on the PROMIS Depression questionnaire, they will follow the Depression Pathway. Participants who score ≥ 60 on both questionnaires will be indicated to follow the Anxiety Pathway, and the digital behavioral health coaches will personalize their care by using some depression management techniques at their discretion.

Participants will have access to the live coach via an asynchronous text messaging component within the application, receiving patient-centered and personalized support. The main goal of the coach is to help guide the participant through the application to apply the techniques into everyday life situations and especially into the perioperative context. Coaches can also personalize the program the participant receives and add techniques from the other program if needed.

Although participants can text the coach anytime, the application is not designed to be a crisis management tool. In case of emergency, participants can use a button available within the app which will direct them to contact *ReSolve* or 911. ReSolve is a crisis-management hotline and walk-in clinic as part of the UPMC.

#### Usual care

The control intervention consists of the usual care of a patient undergoing primary total hip or knee replacement, which includes a surgery-specific education session before surgery. This pre-surgical visit provides a detailed verbal information on the preparation for surgery in terms of nutrition, expectations, breathing exercises, and usual workflow until the day of surgery; surgery itself; and materials used for the replacement and recovery from surgery. Questions and concerns raised by patients are also answered and discussed by the orthopedic surgery nurse coordinator. Patients will also be educated about the potential resources for anxiety and depression management.

### Data collection procedure (recruitment and data collection procedure)

#### Recruitment and retention

Patients scheduled for their pre-operative evaluation at the Center for Perioperative Care clinics or at the orthopedic clinic will be screened for eligibility, and those deemed eligible will be approached by the study coordinators for recruitment or given a flyer by nurse practitioners or physician assistants. Patients who are interested will be able to consent with an investigator or a research coordinator in person, reach out to the research team, and use the QR code that appears on the flyer to give their contact information, or they will be called by a study team member.

Participants will be able to sign the informed consent via REDCap through a virtual interview with the principal investigator or in person with an investigator or research coordinator. In the case of the e-consent, virtual interviews will be conducted remotely using HIPAA-compliant *Zoom* and following a semi-structured format to ensure a systematic yet flexible approach. On the consent form, participants will be asked if they agree to use of their data should they choose to withdraw from the trial. Participants will also be asked for permission for the research team to share relevant data with people from the university taking part in the research or from regulatory authorities, where relevant. This trial does not involve collecting biological specimens for storage.

Once patients provide consent, we will use the PROMIS questionnaires to assess their mood condition and identify those with high levels of anxiety and depression. They will be eligible if they have a *T*-score ≥ 60 on the PROMIS Anxiety Short Form 4a v1.0 questionnaire and/or PROMIS Depression 4a Short Form v1.0 questionnaire. Participants who meet this criterion will be enrolled and randomized into perioperative treatment with a RxWell™ and usual care or only usual care.

To promote participant retention and compete follow-up, the weekly trial meetings will identify potential data loss and prompt the study coordinators and coaches to reach out to subjects to engage them.

#### Surveys employed

The full survey, including the four questionnaires, is expected to be completed in no more than 15 min. REDCap will host all surveys.

#### Data collection

Initially, participants will complete a demographic, lifestyle, and diagnostic survey, consisting of age, gender, ethnicity, race, height, weight, smoking/alcohol use, medical history, ongoing treatments, and comorbidities.

At the baseline, participants from both groups (intervention and education group) will also complete the PROMIS 29+2 v2.0 form, except the Anxiety and Depression subsection since it will have been already completed during the eligibility assessment, the GAD-7 and PHQ-8 scales, the Pain Catastrophizing Scale (PCS), the Knee injury and Osteoarthritis Outcome Score (KOOS), and Hip injury and Osteoarthritis Outcome Score (HOOS) and the Pain Medications Survey and Pain Scores Survey created in REDCap (Table 1).

Participants will be assessed with the same instruments on the day of surgery. In addition, participants allocated in the intervention group will be assessed with the GAD-7 and PHQ-8 bi-weekly through the RxWell™ application during its use.

#### Long-term follow-up

Both groups will be assessed at 1, 2, and 3 months after the surgery, which corresponds to 2, 3, and 4 months after the enrollment. Participants from both groups will have to complete the same instruments described above and the post-surgical survey created in REDCap, which records potential post-surgical complications and additional measures like the length of stay in the hospital, the time to ambulation, and the use of physiotherapy. In addition, participants will also have to complete a satisfaction survey about RxWell™ at the 3-month timepoint, corresponding to the last interaction with the participants. The purpose of this follow-up is to collect data on long-term effects of the interventions and document any changes that might take place in the participant’s disease condition, their frequency of CBI intervention practice, and other additional changes noted.

Users will complete GAD-7and PHQ-8 bi-weekly to monitor their behavioral health over time, and the digital behavioral health coaches will review the scores, free text in each technique, and user message to the coach within two business days. In the event of a risk escalation, coaches will contact the coach supervisor to notify a high-risk situation or an interaction with a user where they encounter concerning symptoms that may be exhibited either within the context of a message sent to the coach or free text within a technique.

As for behavioral studies, trials are commonly designed with a waitlist control group. This approach would allow that all participants have an opportunity to utilize the intervention; however, in the current trial with a focus on feasibility, we will use the randomized approach and plan the waitlisted approach for a larger clinical trial.

The data entry and coding will be performed by study coordinators electronically using the REDCap. All the data are secured behind a firewall within the University of Pittsburgh (Clinical and Translational Science Institute at the University of Pittsburgh Grant Number UL1-TR-001857).

### Data analysis

The primary hypotheses and all other comparisons will be assessed with intention to treat estimates. Between-group differences in primary outcomes, PROMIS anxiety and depression scores, PHQ-8, and GAD-7 scores will be tested using independent two sample *t*-tests on the day of the surgery. Two-sided tests using *p* values of < 0.05 will be considered statistically significant. Differences of tests showing Cohen’s *D* of > = 0.8 will be considered clinically significant. Participants with missing primary timepoint data will be excluded from testing. For secondary outcomes, we will calculate descriptive statistics i.e., usage of RxWell™, adherence, use frequency, etc. Testing of treatment and control group differences in secondary outcomes will be applied to appropriate variables, i.e., participant perioperative pain, opioid equivalent requirement, functional recovery, etc., for time point baseline, day of surgery, and 1 month follow-up. Continuous variables will be described using means and standard deviations. Categorical variables will be described using frequencies/proportions. We will use independent sample *t*-tests and chi-squared analyses to examine between group differences. Fisher’s exact tests and Mann-Whitney *U* tests will be performed in replacement of their counterpart parametric tests where appropriate. Missing data will be removed from denominators, proportions, distributions, and testing of their differences. We will use longitudinal mixed effect models to account for within person variance across all time points as a secondary analysis.

Baseline patient demographics, comorbidities, and procedure details will be stratified by group, and described standardized mean differences will be calculated to compare groups (Table 1). As a secondary analysis, we will use longitudinal mixed effect models to account for within person variance across all time points. We will adjust models using demographics found to have greater than 0.2 standardized mean difference. No subgroup analysis will take place.

We estimated that 50% or more of eligible patients will be enrolled, and as for the proportion of engagement, we are targeting 70% or more of the enrolled patients attending the first SuRxgWell™ orientation class and 50% or more of the follow-up weekly. As for the proportion of compliance, we are targeting 60% or more of the enrolled participants completing the questionnaires; as for the proportion of adherence, we are targeting 60% or more of the enrolled participants who are considered engaged with the app, completing three or more CBT techniques.

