The primary outcome will be day of surgery anxiety or depression symptoms measured with the PROMIS Short Form v1.0 -Anxiety 4a/Depression and Generalized Anxiety Disorder Measure (GAD-7) and Patient Health Questionnaire (PHQ-8). Secondary end points include measuring other health-related quality of life outcomes including sleep disturbance, fatigue, ability to participate in social roles, pain interference, cognitive function, pain catastrophizing, and physical function. Other secondary outcomes include collecting data about preoperative and postoperative pain scores, and pain medication usage, and orthopedic functional recovery at baseline, day of surgery, and 1, 2, and 3 months after the surgery with the Pain Catastrophizing Scale, the Knee injury and Osteoarthritis Outcome Score (KOOS), and Hip injury and Osteoarthritis Outcome Score (HOOS). In addition, subjects will be asked to complete a GAD-7 and PHQ-8 questionnaires bi-weekly (via the *RxWell*™ app for the interventional group or REDCAP for the control group). Data about postsurgical complications, and resource utilization will also be recorded. We will also receive monthly reports measuring the usage and engagement of RxWell use for each participant randomized to that arm. The primary hypotheses will be assessed with intention-to-treat estimates, and differences in primary outcome will be tested using independent two sample *t*-tests. This trial is registered to the ClinicalTrials.gov database (NCT05658796) and supported by the DAPM, UPMC Health Plan, and the NIH.

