## Materials and methods

### Study design

This is a prospective, randomized, controlled clinical trial in a multi-hospital health care system among patients with high levels of anxiety with an indication for primary total hip or knee arthroplasty. We will be comparing two groups: one that receives access to RxWell™ and usual care and one that only receives the usual care. Figure 1 and Table 1 show the study design, timing of pre- and postoperative use of RxWell™, and follow-up evaluations. CONSORT 2010 items and CONSORT-SPI 2018 checklist are presented for the abstract (Table 2) and main text (Table 3). The SPIRIT Checklist is presented as an additional file (Additional file 1). We will recruit patients from 4 hospitals within the *UPMC system* (*UPMC Shadyside*, *Magee*, *East*, and *Passavant hospitals*). In this pilot, randomized feasibility trial, we will prospectively allocate 34 subjects in the control group, and using a 1:3 allocation, we will have 102 in the intervention group (two-sided *t*-test with alpha of .05, power of .8, with a 3:1 ratio and a 50% drop out rate for a Cohen’s *d* of .8). A block randomization schedule generated using the R software (version 4.2.1, R Core Team, 2022) will be used to allocate the participants to either dCBI plus usual care (*intervention*) or usual care (*control*) with a 3:1 allocation (Table 2). Investigators will be blinded for group assignment in REDCap, and they will also be blinded for the monthly reports. Research coordinators, the statistical data analysts, and subjects will not be blinded. To make sure investigators are blinded to the intervention, investigators will not have access to the randomization table and surveys in REDCap. Investigators will only be able to access the eligibility checklist and informed consent surveys in REDCap. Patients will be randomized immediately after the PROMIS Anxiety 4a and the PROMIS Depression 4a patient assessment by a research coordinator using REDCap. We do not anticipate any requirement for unblinding, but if required, the director of clinical research operations, regulatory specialist, study coordinators, or the principal investigator will have access to group allocations and any unblinding will be reported.

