#### Sample size calculation

This is a pilot study meant to inform a subsequent RCT based on this treatment. We will determine if the study is a success if this effect size is observed in our primary outcomes and thus our study is powered based on these effects. From observed estimates in concurrent studies, we expect a clinically significant effect size of Cohen’s D greater than or equal to 0.8. Our primary analysis is comparing PROMIS T scores, GAD-7 and PHQ-8 between groups on day of surgery. Therefore, with 95% confidence, 80% power, using two sided tests and assuming a 50% retention rate, our desired sample size is 136. We will utilize 1:3 allocation, randomizing 34 to the control group and 102 to the intervention group. We are allocating 1:3 to get more accurate estimates around within treatment group improvements as well as to increase the number of patients we can potentially aid by supplying them with the low-risk treatment. The 1:3 allocation was chosen based on the study design and the nature of the intervention. This is a proof-of-concept study in which we want to evaluate the feasibility of RxWell™. In addition, our target subjects are patients with a moderate level of anxiety and/or depression, and we consider it is more ethical to offer a treatment to as many subjects as possible. Sample size calculations were conducted using the Power Analysis and Sample Size Software (PASS - 2022). NCSS, LLC. Kaysville, Utah, USA.

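### Four primary scales are each tested at p < 0.05 with no any/all rule, on a sample size for one test; neither reading gives both 5% error and 80% power

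*Protocol article*

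**What the plan says.** - **Tests.** Data analysis: "Between-group differences in primary outcomes, PROMIS anxiety and depression scores, PHQ-8, and GAD-7 scores will be tested using independent two sample". These are day-of-surgery t-tests. In the same section, p "values of < 0.05 will be considered statistically significant". It sets no order of testing, adjustment or joint rule.
- **Sample size.** The Sample size calculation section also names the PROMIS T-scores, GAD-7 and PHQ-8 on the day of surgery as the primary analysis. Its basis is one comparison: "we expect a clinically significant effect size of Cohen’s D greater than or equal to 0.8", "using two sided tests and assuming a 50% retention rate, our desired sample size is 136", and "randomizing 34 to the control group and 102 to the intervention group". Study design gives the same inputs: "with alpha of .05, power of .8, with a 3:1 ratio and a 50% drop out rate".
- **Success rule.** The Sample size calculation section calls the study a success if this effect size is seen in the primary outcomes. It does not say in any of them or in all.
- **Abstract.** "The primary outcome will be day of surgery anxiety or depression symptoms measured with the PROMIS Short Form v1.0", followed by GAD-7 and PHQ-8. The conjunction is anxiety or depression.
- **Time points.** The Primary outcomes section defines the primary outcome as the four scores one month before surgery, then "on the day of the surgery, and 1, 2, and 3 months after surgery, to assess the severity". The abstract, the Sample size calculation and Data analysis all use the day of surgery.

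**The concern.** With four co-equal primary tests, the meaning of a positive trial depends on a rule that the article does not state. If one significant scale suffices, the overall chance of a false finding exceeds the level at which each test is run. If all four must be significant, the power falls below the planned 80%. The sample size fits neither case.

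Two features raise the stakes. The trial is meant to inform a later randomised trial, so a conclusion resting on the most favourable of four scales would carry into that design. And Study design states that the statistical data analysts are not blinded, so a rule fixed in advance is the main protection against choosing the scale after seeing results.

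**Working it through.** **Inputs.** From the article: two-sided alpha 0.05, power 0.80, d = 0.8, 3:1 allocation, 50% retention, 34 control and 102 intervention, four primary scales. Not in the article: the correlation between the scales. It is assumed equal for all pairs and varied.

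**1. The plan's own figure.** For one test with allocation ratio 3,

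n(control) = (1.960 + 0.842)² × (1 + 1/3) / 0.8² = 7.85 × 1.333 / 0.64 = 16.4, rounded up to 17.

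Intervention: 3 × 17 = 51. Evaluable: 68. Randomised: 68 / 0.5 = 136, an exact match. Noncentral-t power at 17 and 51 is 80.4%. So 136 is the size for one test at 5%.

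**2. Four tests, independent.** 1 − 0.95⁴ = 18.5%.

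**3. Four tests, correlated.** Simulation of 17 versus 51 evaluable, four equally correlated normal outcomes and pooled t-tests, with 60,000 trials per setting. Repeat runs differ by a few tenths of a point.

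| Assumed correlation | No effect: at least one p < 0.05 | No effect: at least one p < 0.05 favouring treatment | d = 0.8 on all four: all four p < 0.05 |
|---|---|---|---|
| 0.3 | 17.6% | 8.9% | 50% |
| 0.5 | 15.8% | 7.8% | 56% |
| 0.7 | 13.2% | 6.7% | 62% |
| 0.8 | 11.6% | 5.8% | 66% |

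Under no effect, all four are significant together in 1% of trials or fewer across this range, so an all-must-win rule needs no adjustment. Its cost is power.

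**4. The d ≥ 0.8 success rule.** The smallest observed d that reaches p < 0.05 at 17 and 51 is t(0.975; 66 df) × √(1/17 + 1/51) = 1.997 × 0.280 = 0.56. An observed d of 0.8 is therefore a higher bar. Under no effect, at least one of four scales reaches it in favour of treatment in about 0.8% to 1.2% of trials (correlation 0.8 to 0.3).

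**5. The remedies, with d = 0.8 on all four scales.**

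| Rule | Power per scale | Power for at least one |
|---|---|---|
| One named primary at 0.05 | 80.4% | not applicable |
| Four at 0.05/4 (Bonferroni) | 61.5% | 79% to 93% |
| Four under Holm | about 69% to 72% | 79% to 93% |

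Bonferroni and Holm share the same first step, so their power for at least one rejection is identical.

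**The case against.** **The any-one-wins rule is inferred.** This stands. No section says that one significant scale is enough. The abstract's wording points that way but may only echo the and/or eligibility criterion. That is why both readings are worked through; under the other one the problem moves from error to power.

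**The 5% is a per-test level, and as such it holds.** Also true. The article states no family-wise rate. A reader might infer that the trial's false-positive rate is simply two to three times 5%. The documents do not support that as a fact, since the multiple depends on the any-of reading and on a correlation they do not give. The two-sided figure also counts results against treatment; false benefit is about 6% to 9%.

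**The declared success rule is not inflated.** This stands: about 1% on any scale. The concern is limited to claims based on p < 0.05, which Data analysis defines separately from clinical significance.

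**Time points.** A reader might multiply four scales by the time points in the Primary outcomes section and infer a far larger error. The documents do not support this. The abstract, the Sample size calculation and Data analysis all fix the day of surgery, and models across all times are labelled secondary. The list also includes baseline, which cannot be an effect endpoint, so it reads as a measurement schedule. What remains is a wording conflict.

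**All four scales in everyone, though each participant follows one pathway.** This is no defect. The coaches may add techniques from the other programme, so comparing both constructs in all participants is coherent.

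**It is a pilot, and an analysis plan might add a hierarchy.** The pilot status lowers the severity. It does not remove the point, because the article powers the trial on these tests and sets a significance threshold for them. A hierarchy set elsewhere would still leave this text to be amended.

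**Conclusion.** The point holds as a missing decision rule. Four primary scales are each tested at 0.05 on a sample size for one test:

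- **Any one suffices:** about 11.5% to 17.5% chance of at least one false p < 0.05 (18.5% if independent), of which about 6% to 9% is false benefit.
- **All four required:** error is controlled, but power is about 50% to 66%, not 80%.

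These ranges assume 17 and 51 evaluable participants, normal outcomes and an equal between-scale correlation of 0.3 to 0.8. The power figures also assume d = 0.8 on every scale. The observed d ≥ 0.8 rule keeps false success near 1%, but it has the same any/all gap. Severity: should be fixed. The trial is a pilot, but it runs powered hypothesis tests.

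**What to change.** 1. Choose one of two rules.
   - **One primary scale on the day of surgery, the other three secondary.** No alpha cost; 136 and 80% power stand. A primary based on the scale that sets the participant's pathway is possible but optional.
   - **Four primaries under Holm at an overall 5%, with power restated.** Per-scale power falls from 80.4% to about 69% to 72%, a loss of about 9 to 11 points; power for at least one scale is 79% to 93% (d = 0.8 on all four).
2. State whether the d ≥ 0.8 success rule applies to the named scale, to any scale or to all.
3. Reword the Primary outcomes section so that the day of surgery is the primary time point and the others are a measurement schedule or secondary, in line with the abstract, the Sample size calculation and Data analysis.

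With a single primary the cost is wording only. Under Holm it is wording plus the disclosed loss of per-scale power. Either choice should be fixed before outcome data are examined by group.

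### Function (HOOS/KOOS) is compared between arms in a mixed hip and knee population without adjusting for joint or baseline score, which can cost precision on a secondary outcome

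*Protocol article*

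**What the plan says.** - **Population.** The abstract's Methods restrict entry to primary, unilateral hip or knee arthroplasty, so each patient has one operated joint.
- **Instrument.** Table 1 lists HOOS/KOOS as a single functionality measure. The Data collection section says that participants of both groups complete, among other forms, "the Knee injury and Osteoarthritis Outcome Score (KOOS), and Hip injury and Osteoarthritis Outcome Score (HOOS"). The same instruments return on the day of surgery and, under Long-term follow-up, at 1, 2 and 3 months. No section ties a scale to the joint.
- **Test.** The Data analysis section compares arms on "participant perioperative pain, opioid equivalent requirement, functional recovery, etc., for time point baseline, day of surgery, and 1 month follow-up". The method is the independent-sample t-test, with Mann-Whitney as the fallback, and no covariates.
- **Models.** Longitudinal mixed models are a secondary analysis. They adjust for demographics whose standardized mean difference exceeds 0.2. Procedure details are summarised by group with standardized mean differences but are named separately from demographics and do not appear in the adjustment rule.
- **Subgroups.** "No subgroup analysis will take place".
- **Available data.** Type of operation is recorded (Other variables of interest), and HOOS and KOOS are collected at baseline (Data collection). Randomization is described as blocked, with no stratification by joint stated (Study design).

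**The concern.** Better functional recovery is one of the four postoperative benefits hypothesised at the end of the Background. The population combines two operations and the function measure combines two joint-specific questionnaires, yet the stated test uses neither the joint nor the patient's own starting score.

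Two losses are possible. If each patient contributes one operated-joint score and hip and knee patients differ in mean, that difference sits in the error term. If the Data collection wording is followed literally and each scale is compared in everyone, part of each comparison concerns a joint that was not operated on, and the arm difference shrinks. In either case the standardized effect would tend to fall below the 0.8 that the Data analysis section calls clinically significant, in a pilot meant to inform a later trial.

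The plan does name an outcome-specific covariate where it wants one: resource use is adjusted for surgical decision (Secondary outcomes). It names none for function.

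**Working it through.** **Step 1. The plan's own sample size.** Inputs: "alpha of .05, power of .8, with a 3:1 ratio and a 50% drop out rate" (Study design); "with 95% confidence, 80% power, using two sided tests", Cohen's "D greater than or equal to 0.8" and "assuming a 50% retention rate, our desired sample size is 136" (Sample size calculation).

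Controls = (1 + 1/3) × (1.960 + 0.842)² / 0.8² = 1.333 × 7.85 / 0.64 = 16.4, rounded up to 17. Intervention = 3 × 17 = 51. Dividing by 0.5 retention gives 34 and 102, total 136. This matches the plan: "randomizing 34 to the control group and 102 to the intervention group". Noncentral-t power is 0.804 at 17 v 51 and 0.779 at 16 v 48.

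This calculation concerns the day-of-surgery mood scores. Below, d = 0.8 and 17 v 51 are borrowed for function as an illustration.

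**Step 2. Power formula.** Two-sided 0.05, 66 degrees of freedom, noncentrality d / √(1/17 + 1/51) = d / 0.280.

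**Step 3. One operated-joint score per patient, joint ignored.** Let g be the hip-knee difference in mean, in within-joint SDs, and p the knee share. The documents give neither. The SD becomes √(1 + p(1−p)g²), and d becomes 0.8 divided by it. At p = 0.5:

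| g | SD factor | d | power |
|---|---|---|---|
| 0 | 1.000 | 0.800 | 0.80 |
| 0.25 | 1.008 | 0.794 | 0.80 |
| 0.5 | 1.031 | 0.776 | 0.78 |
| 0.75 | 1.068 | 0.749 | 0.75 |
| 1.0 | 1.118 | 0.716 | 0.71 |

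At p = 0.6 the last row is 0.715, so the knee share matters little here.

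**Step 4. Chance imbalance is already counted.** The arm difference in knee share has SD √(0.25 × (1/17 + 1/51)) = 0.140. At g = 1 it contributes variance 0.140² = 0.0196 to the arm difference. The within-joint part is 0.280² = 0.0784. The sum is 0.0980, whose root 0.313 equals 0.280 × 1.118. The imbalance is therefore the same variance that the SD factor in Step 3 adds. Under randomization it is not bias.

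**Step 5. Each scale compared in everyone.** Assume an effect of 0.8 on the operated joint's scale, none on the other, and equal SDs. Then d = 0.8 × the share with that joint operated.

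| Knee share | Scale | d | power |
|---|---|---|---|
| 50% | KOOS or HOOS | 0.40 | 0.29 |
| 60% | KOOS | 0.48 | 0.39 |
| 60% | HOOS | 0.32 | 0.20 |

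**Step 6. What adjustment returns.** Including joint removes the g term in Step 3. Including the baseline score multiplies the residual variance by about 1 − r², where r is the within-joint correlation of baseline with follow-up. The documents give no r, so no figure is put on that gain. The two covariates take the error degrees of freedom from 66 to 64.

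**The case against.** The best case for the plan is that little here is fixed wrongly. Which form each patient is scored on is the kind of detail an analysis plan supplies, and none is shown. The Data collection sentence may be shorthand for the form that fits the joint, and the single HOOS/KOOS line in Table 1 fits that reading. The Data analysis section never says that KOOS will be compared in hip patients. Function is one of many secondary outcomes in a pilot and was never powered. Most of this stands. The absence of a scoring rule is not a finding by itself, and a fall from 80% is a fall from a level that the plan never claimed for function.

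A reader might infer more than the text supports:

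- **That every reading loses power.** It does not. A pooled operated-joint score loses essentially nothing when hip and knee means are within about 0.25 SD.
- **That excluding subgroup analysis blocks a proper analysis.** Scoring by operated joint defines the outcome, and joint as a covariate is an adjustment. Neither is a subgroup analysis. Separate hip and knee tests would have power of only 0.42-0.57 each at 50-60% knees, but the plan does not propose them.
- **That hip/knee imbalance biases the estimate.** It adds variance only (Step 4).
- **That type of operation is ignored altogether.** If it counts among the procedure details, it is described by arm with standardized mean differences.

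What the objection does not remove is the stated analysis: an unadjusted test, and models whose adjustment rule covers demographics only. An analysis plan that followed this text would leave joint and baseline score out. The baseline value might enter the mixed model as one of the repeated measurements, but no comparison names it as a covariate.

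**Conclusion.** The point holds in a limited form. The stated comparison of function leaves out two strong candidate covariates that are already collected, and the wording on who completes which scale needs one clarifying clause.

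On the more natural reading, one operated-joint score per patient, ignoring joint costs between 0 and about 9 percentage points of power for a hip-knee gap of 0 to 1 SD. The further loss from ignoring baseline cannot be sized from the documents. The large loss, with power of 20-39%, arises only if each scale is compared in all patients. It also rests on zero effect on the unoperated joint's scale (a partial effect would shrink it), equal SDs and 50-60% knees.

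All figures use d = 0.8, set for the mood outcomes, and 17 v 51 evaluable patients, here assumed to apply to function as well. The primary analysis and the total of 136 are untouched. The change is worth making because it is nearly free, not because the trial is at risk.

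**What to change.** 1. **Data collection:** state that each patient is scored on the scale for the operated joint, HOOS for hip and KOOS for knee arthroplasty.
2. **Data analysis, function:** replace the unadjusted t-test with one arm comparison in all patients at each follow-up time point tested, using a linear model with arm, joint (hip/knee) and the baseline value of that score.
3. **Data analysis, mixed model for function:** add joint as a prespecified covariate, whatever its standardized mean difference. A short note that this is adjustment and not subgroup analysis would prevent confusion with the existing exclusion.

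Cost: wording, and two degrees of freedom (66 to 64 with 68 evaluable patients). No new data are needed. If only the operated-joint form is handed out, patients complete one questionnaire fewer at each visit. The price in interpretation is that a single pooled comparison assumes a similar arm effect on the two scales.
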